### Assessments

Table 1 summarizes the different parameters used at each measurement point.

#### Questionnaires

Approximate duration of questionnaires completion is 40–50 min at each measurement point.

##### General Information

Sociodemographic and medical data (gender, age, education level, professional activity, spiritual believes, personal history of cancer and treatment, possible recurrence during the study) will be collected. The Big Five Inventory (short version—10 items; Courtois et al., 2020) will also be administered. This questionnaire aims at rapidly assessing personality according to the 5 domains of the original Big Five Inventory (extraversion, conscientiousness, negative emotionality, open-mindedness, and agreeableness).

##### Physical and Psychological Functioning

*Visual Analogue Scales (VAS)*: Different VAS will assess the participants’ emotional state (pain, empowerment, fatigue, emotional distress, sleep difficulties). VAS will also be used during the duration of the group intervention to assess the severity of fatigue, distress, sleep difficulties, and pain on a weekly basis. Each score will be comprised between 0 and 10.*Multidimensional Fatigue Inventory* (MFI-20; Smets et al., 1995): This 20-item scale is designed to measure fatigue on 5 different dimensions: general fatigue, physical fatigue, mental fatigue, reduced motivation, and reduced activity.*Insomnia Severity Index* (ISI; Savard et al., 2005): This 7-item questionnaire investigates the sleep complaints and the associated distress.*Hospital Anxiety and Depression Scale* (HADS; Zigmond and Snaith, 1983): This 14-item scale measures anxiety (7 items) and depression (7 items) and has been validated for people with somatic illnesses.*Mental Adjustment to Cancer Scale* (MAC; Watson et al., 1988): This questionnaire assesses the coping styles and adjustment to cancer. It is divided into two sub-scales: positive and negative adjustments.*Cognitive Emotion Regulation Questionnaire* (CERQ; Garnefski et al., 2001): This multidimensional scale investigates the cognitive emotion regulation strategies used after experiencing negative events linked to the disease or its treatments.*Multidimensional Psychological Flexibility Index* (MPFI-24; Grégoire et al., 2020b): This 24-item scale assesses the psychological flexibility and psychological inflexibility, through 12 dimensions (6 linked to psychological flexibility: acceptance, present moment awareness, self as context, defusion, contact with values, committed actions; and 6 for psychological inflexibility: experiential avoidance, lack of present moment awareness, self as content, fusion, lack of contact with values, inaction) and 2 total scores (psychological flexibility and inflexibility).*Life events*: To assess whether the participants experienced any major life event during or after the intervention, we will ask them the following question (yes/no): “*Did you experience any major life event since the last time you completed these questionnaires* (wedding, birth, job loss, accident, health problem, etc.).”

##### Cognitive Functioning

*Functional Assessment of Cancer Therapy – Cognitive Function* (FACT-Cog v.3; Joly et al., 2012): This 20-item questionnaire measures the participant’s subjective cognitive functioning over the past week.

##### Questionnaires Linked to the Chosen Intervention (Hypnosis, Meditation or SICT)

*VAS (/10)* concerning the expectations and motivation to participate in the intervention (T0), then concerning the quality of the relationship with the therapist (T1–T3).*Questions about the chosen intervention (free text)*: This will aim at investigating the personal definition of hypnosis, meditation, or SICT of participants, their beliefs and *a priori* concerning the intervention they will participate in.*Creative Experiences Questionnaire* (CEQ; Merckelbach et al., 2001): This 25-item (true/false) scale has been designed to investigate the fantasy proneness. Questions are about, for examples, imaginative friend or animal, belief in supernatural beings, tendency to dream of fantasize, or out-of-body experiences.*Free recall of an intense hypnosis/meditation/SICT episode (intense autobiographical episode for the participants in the control group)*: This will be used to collect phenomenological data about each non-ordinary state of consciousness involved in the study. As patients in the control group will not participate in any of the interventions, they will have to describe an important autobiographical memory that happened during the study (e.g., wedding, birth). The recall of the episode will have to be as detailed as possible.*Memory Characteristics Questionnaire* (MCQ; Johnson et al., 1988): This 16-item questionnaire is adapted from the original questionnaire. It assesses a wide range of memory characteristics (visual details, complexity, spatial, and temporal information, feelings). Participants will be asked to answer the questionnaire while thinking about one specific memory (the one used in the free recall).*Revised Mystical Experience Questionnaire* (MEQ30; Maclean et al., 2012): This 30-item scale is designed to assess the mystical characteristics of a specific episode or memory (in this study, a hypnosis, meditation, or SICT episode), across four factors: mystical, positive mood, transcendence of time/space, and ineffability.*Presence questionnaire* (Heck et al., 2021): This 12-item scale has been initially designed to measure the feeling of presence after the use of virtual reality. As the original questionnaire was focused on the virtual environment specific to virtual reality, we adapted it to a more general “suggested” environment, such as in hypnosis, meditation, and SICT. Questions are about the impression to have been present in the environment, to have interacted with it, or to have felt the presence of other people in it, for examples.

#### Neurophysiological and Biological Measures

We will record an electroencephalogram (EEG) resting state (256 EGI, Geodesics) during 15 min, combined (T1 and T3) or not (T0) with an EEG during hypnosis, meditation, or SICT state (15 min). During each EEG, we will also record an electrocardiogram (ECG) and an electromyogram (EMG), and measure the breathing (effort and pressure, Polygraph Input Box of EGI system) and body temperature. Tumor marker rates (according to the patient’s diagnosis) will also be collected in the patient’s medical record or based on their blood test results.

### Data Coding and Storage

Most questionnaires will be completed electronically (on www.alchemer.com) by the participants, through a secured link sent by the experimenters. Data encoding will be done automatically by Alchemer and will be regularly checked by the experimenters. Final databases and manually coded data (e.g., from manually completed questionnaires or directly collected from medical records) will be stored on a protected server from the University, protected by a password. Data coding and storage comply with the General Data Protection Regulation (GDPR).

### Statistical Analyses

Baseline (T0) demographic, medical, and psychological data will be compared between groups to test for initial groups equivalency using inferential statistics, including ANOVAs and chi-square tests. Normality of data will be checked using Shapiro–Wilk test. Group-by time changes, and pre- and post-assessment comparison of each variable within each group will be assessed using repeated measures MANOVA followed by post hoc comparisons, on the participants who completed all the needed assessments points. Hierarchical linear regressions will be conducted to investigate the factors associated with the evolution of our main outcomes. All tests will be two-tailed, and the alpha will be set at 0.05. For EEG data analysis, MATLAB, EEGLAB, FieldTrip, Brainstorm, and in-house MATLAB and Python modules will be used. EEG signal will be preprocessed as in our previous works [downsampling, epoching, filtering, removing noise (notably using ICA), channels interpolation, re-referencing; Carrière et al., 2020; Thibaut et al., 2021]. EEG markers will then be extracted: spectral (e.g., power spectrum density), connectivity (e.g., weighted symmetrical mutual information), complexity (e.g., permutation entropy; Engemann et al., 2018). We will also apply graph theory connectivity measures to further assess changes between brain regions (Chennu et al., 2017; Carrière et al., 2020; Thibaut et al., 2021). Results will be corrected for multiple comparisons and considered significant at *p* < 0.05. Statistical analyses will be performed after all data have been collected for T2, then for T3 and T4.

All participants will be informed by e-mail about the final results of the study. Scientific publications and presentations will also be planned.

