**Methods and analysis:**

A power analysis required a total sample of 160 patients. Main inclusion criteria are: cancer diagnosis, active treatments completed for less than a year, no practice of hypnosis, meditation, or SICT, and presence of at least one of these four symptoms: fatigue, sleep difficulties, depression, or anxiety. Each participant will choose the intervention in which they want to participate (hypnosis, mindful self-compassion meditation, SICT, or no intervention—control group). To test the effectiveness of the interventions, data will be collected by questionnaires and neurobiological measures and directly from the medical record at four time points: before inclusion in the study (baseline); immediately after the intervention; and at 3- and 12-month follow-up. The longitudinal data in each group will then be measured.

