## Methods and Analysis

### Design

We designed a longitudinal controlled superiority trial (see Figure 1) with 160 patients with cancer who will choose between four conditions (see section “Recruitment” for sample size calculation): hypnosis-based group intervention, MSC meditation-based group intervention, SICT-based group intervention, or a control group. This kind of design has been chosen because patients who receive their preferred therapeutic option seem to be more motivated and exhibit greater adherence to the treatment (King et al., 2005; Preference Collaborative Review Group, 2008; Sedgwick, 2013; Bicego et al., 2021a). Indeed, preference-based trials are increasingly developed as researchers often want to know if an intervention is effective for the participants who choose it, rather than determining the best treatment option irrespective of the participant’s choice (Kowalski and Mrdjenovich, 2013). In addition, pragmatic trials are also more and more developed and aim at assessing the effects of interventions in real-life routine practice conditions, rather than under optimal conditions. The results from a pragmatic trial can be generalized and applied in routine practice (Patsopoulos, 2011). Moreover, one of our previous study with oncological patients showed that different intervention groups, based on participants’ preferences, were similar at baseline on the sociodemographic, medical, and clinical data investigated (Grégoire et al., 2017). Participants will then know in which group they belong and will be aware of the existence of the other intervention groups.

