The recruitment started in December 2020 and is ongoing. Sample size has been determined by a power analysis allowing a comparison between the four groups. The sample size calculation was based on a repeated measures ANOVA (“between factors”). Alpha was set at 0.05, power at 90%, the standardized effect size at 0.3 and the expected correlation between repeated measures at 0.6. These coefficients were successfully used in our previous studies (Grégoire et al., 2017, 2020a). As there will be four groups and four measurements times, a total of 116 patients will be needed according to this analysis. Based on our previous experience with a similar design, we expect a 20% drop-out rate, leading to a sample of 140 patients (35 in each condition; Grégoire et al., 2020a). As our group sessions will include approximately 10 persons, we will then aim at recruiting 40 participants in each condition (i.e., four groups of 10 participants in hypnosis, MSC meditation, and SICT groups and 40 participants in the control group), for a final sample of 160 participants. Participants will have the opportunity to choose the intervention in which they want to participate. Most of the participants already have a strong preference for one of the three interventions when contacting us. However, each interested person who fill the inclusion criteria will be asked to watch a short video we made to explain the three interventions and the aims of the study.^1^ This allows every participant to receive standardized information about the study and to make or confirm their choice of intervention. However, once 40 participants have been recruited in a condition, it will not be possible for other interested persons to be included in this condition. These persons will be proposed to integrate the control group or another active condition.

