**Hypnosis, MSC meditation, and SICT will have positive overall benefits on the quality of life of cancer patients**, with increased effects over time. More specifically, we expect that the three interventions will have superior positive effects on the patients’ quality of life than the control group. We expect that these effects will be significant right after the intervention (T1) and will stay stable or increase at 3- and 12-month follow-up (T2 and T3) due to continued practice. Moderate difference might be observed between the three intervention groups. For example, SICT could impact more the body-related variables (e.g., pain and fatigue) as it involves the body more directly (e.g., in the induction process). We expect that a small improvement will be achieved in the control group as well, but much weaker than in the three intervention groups.**Phenomenological experiences will change over time and will be intervention-dependent**. We hypothesize that over time and in the three intervention groups, phenomenology will become more joyful and richer. As the phenomenology of hypnosis, MSC meditation, and SICT has been very little studied, we do not have any specific hypothesis concerning the phenomenological differences between the three interventions. Our analyses are exploratory. We however expect that the phenomenology will change in each intervention group between the different measurement times, as the participants are expected to continue to practice regularly after the intervention. We do not expect any major evolution of the phenomenological experiences in the control group.**Neurophysiological changes will be different between the three intervention groups**. We hypothesize that neurophysiological changes will vary according to the intervention and that they will evolve over time, in response to the continued practice of the participants after the intervention. Previous studies showed increased theta power and changes in gamma activity during hypnosis (Vanhaudenhuyse et al., 2020) and increased alpha and theta power, during meditation (Lomas, 2015; Brandmeyer et al., 2019). We hypothesize to observe the same patterns in our study. We do not expect any evolution of neurophysiology in the control group. We also expect differences in neurophysiological correlates of resting state, depending on patients’ clinical outcomes, especially long-term ones. For example, we could expect slower activity if patients are feeling less anxious.**We will be able to confirm, at least in part, the biopsychosocial model of hypnosis**, and MSC meditation and SICT responsiveness mechanisms will be in part similar to the ones implied in hypnosis responsiveness. We also expect other potential factors (linked to body physiology: temperature, ECG, EMG, breathing) to correlate with hypnosis, MSC meditation, and/or SICT responsiveness.

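### Group-by-time tests and within-group pre-post tests stand side by side, and nothing makes the comparison with control the one that decides effectiveness

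*Protocol article*

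**What the plan says.** The Statistical Analyses section of the protocol article gives one sentence to two kinds of test. It opens with group-by-time changes and continues: "pre- and post-assessment comparison of each variable within each group will be assessed using repeated measures MANOVA followed by post hoc comparisons". Both kinds are run among participants who completed the needed assessments, two-tailed at 0.05. Group-by-time comes first, but neither test is called decisive, and the post hoc comparisons are not specified.

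The Methods and analysis paragraph of the Abstract introduces the test of effectiveness, describes data collection, and closes with "The longitudinal data in each group will then be measured". It names no comparison with control.

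Elsewhere the question is comparative. The Design section states "We designed a longitudinal controlled superiority trial". The hypotheses in the Discussion say "we expect that the three interventions will have superior positive effects" relative to control, and add "We expect that a small improvement will be achieved in the control group as well, but much weaker than in the three intervention groups".

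**The concern.** A pre-post test in one arm measures recovery plus any intervention effect and cannot separate the two. Recovery is plausible here. Under Eligibility, patients enter within a year of finishing active treatment and must score at least 4 out of 10 on one of four symptoms, so both natural improvement and regression to the mean are likely. The authors themselves expect some improvement in controls.

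The group-by-time test does not close the gap alone. With four groups and four times it has (4 − 1) × (4 − 1) = 9 degrees of freedom, and it can be significant because two interventions differ from each other. If the follow-up tests are within-arm, the reader still does not learn which intervention beats control. Finding significance in one arm and not in control is not a test of their difference either.

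At stake is a superiority trial that could report an intervention as effective when its patients improved no more than controls did.

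**Working it through.** **Inputs from the protocol article**
- Recruitment: "Alpha was set at 0.05, power at 90%, the standardized effect size at 0.3 and the expected correlation between repeated measures at 0.6"; four groups, four times, 116 patients required, 20% drop-out, target of 40 per condition.
- Statistical Analyses: two-tailed tests at 0.05.
- Completers per arm: 40 × (1 − 0.20) = 32.

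**Assumption.** All arms share the same recovery d from T0 to T1, in baseline SD units, and no intervention has any effect. The article calls the expected control improvement small and gives no figure, so d = 0.1, 0.2 and 0.3 are shown.

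**Step 1: the plan's own figure.** For the between factor, reading 0.3 as Cohen's f, the noncentrality is λ = f²·N·m / [1 + (m − 1)ρ]. With N = 116, m = 4 and ρ = 0.6, λ = 0.09 × 116 × 4 / 2.8 = 14.9. With 3 and 112 degrees of freedom the power is 0.905. The smallest N with 90% power is 115, or 116 with equal groups, so the stated 116 reproduces. The test used for sizing is neither of the two tests in the analysis sentence, so it does not settle which one decides.

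**Step 2: pre-post test in one ineffective arm.** For a paired t-test, dz = d / √[2(1 − ρ)] = d / √0.8, and the noncentrality is dz·√32. The table gives the chance of a significant result in the favourable direction. The Bonferroni column uses 0.05/6, six being the number of pairs among four time points (4 × 3 / 2).

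| d (SD) | noncentrality | uncorrected | Bonferroni, six contrasts |
|---|---|---|---|
| 0 | 0 | 2.5% | 0.4% |
| 0.1 | 0.63 | 8.9% | 2.1% |
| 0.2 | 1.26 | 23.1% | 7.5% |
| 0.3 | 1.90 | 45.2% | 19.9% |

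**Step 3: difference in change against control, same scenario.** In 20,000 simulated trials with 32 per arm, the two-sided test was significant in 4.9% (d = 0.2) and 5.0% (d = 0.3). About half of that is in the favourable direction, so the like-for-like comparison with Step 2 is about 2.5%.

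**Step 4: significant in an intervention arm, not in control.** For one arm the simulation gave 17.5% at d = 0.2 and 25.1% at d = 0.3. For at least one of three arms, treated as independent and uncorrected, the chance is [1 − (1 − p)³] × (1 − p):
- d = 0.1: 0.244 × 0.911 = 22%
- d = 0.2: 0.546 × 0.769 = 42%
- d = 0.3: 0.835 × 0.548 = 46%

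**The case against.** A reader might infer that the within-group tests are themselves planned as proof of effectiveness. The article does not say so. The analysis sentence opens with group-by-time changes, which is the safeguard. The design is labelled a superiority trial, the sample size was set for a comparison of the four groups, and the hypotheses measure the interventions against an expected improvement in controls. The Abstract sentence is compressed and speaks of measuring, not testing. That part of the objection stands.

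The percentages also need care. A reader might take the uncorrected chance that at least one of three ineffective arms is significant (24%, 55% and 84%) as the rate of false claims. Those figures ignore that control would often be significant too, and they assume both the recovery size and no correction. Post hoc tests run only after a significant interaction would give lower rates. The section does promise correction for multiple comparisons, but the promise follows the EEG methods and its reach to the questionnaires is unclear. Correction lowers the rate without changing what is being tested.

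Two further points are fair. Ranking of tests is often left to an analysis plan, which is not shown. The point here, however, rests on what the article does fix: significance tests of every variable within every group, placed level with the comparison that answers the question. And because patients choose their group, the contrast with control is itself open to confounding. That does not rescue the within-arm test, which has no guard against recovery at all.

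**Conclusion.** The concern holds in a limited form. The article plans the right kind of test but does not make it decisive. It sets beside it a test that cannot separate recovery from effect, and its Abstract describes only the within-group course. It does not state that a within-group result alone would count as effectiveness.

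If within-arm p-values did carry the conclusion, an ineffective arm would appear to work on a given outcome in about 9% to 45% of trials uncorrected, or about 2% to 20% with the six-contrast correction, against about 5% two-sided for the contrast with control. These figures rest on 32 completers per arm, the plan's correlation of 0.6 and an assumed shared recovery of 0.1 to 0.3 SD. This should be changed, because it removes a route to a biased conclusion at almost no cost.

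**What to change.** For the clinical outcomes (fatigue, emotional distress, sleep, pain and cognition), state in Statistical Analyses that effectiveness claims rest on three contrasts, each intervention minus control, in change from T0 at T1, T2 and T3, estimated from the group-by-time model. Report within-group changes in these outcomes as means with 95% confidence intervals, labelled descriptive. Reword the Abstract sentence to say that changes will be compared between each intervention group and the control group.

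Within-group analyses of phenomenology and of EEG during the induced state may stay as exploratory. Change in phenomenology within the intervention groups is a stated hypothesis, and Table 1 shows that the induced-state EEG is recorded only in intervention participants.

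The cost is wording: no new patients, data or model. The downside is fewer p-values to report.

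### Superiority over control is tested through an omnibus group-by-time MANOVA, with no active-versus-control contrast named as the confirmatory test

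*Protocol article*

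**What the plan says.** - **Aim.** The Design section states "We designed a longitudinal controlled superiority trial" with three interventions and a control group. The first hypothesis in the Discussion is that "the three interventions will have superior positive effects on the patients" (on quality of life, relative to control). The effect is expected at T1 and should hold or grow at T2 and T3. Moderate differences between the interventions are allowed for.
- **Test.** Under Statistical Analyses, group-by-time changes and within-group pre-post comparisons of each variable "will be assessed using repeated measures MANOVA followed by post hoc comparisons", in participants with all needed assessments. The same section adds: "All tests will be two-tailed, and the alpha will be set at 0.05". It does not say which post hoc comparisons will be made, how they are adjusted, or whether they require a significant omnibus result.
- **Sample size.** The Recruitment section uses the between-factors form of a repeated measures ANOVA, with "the standardized effect size at 0.3" and "the expected correlation between repeated measures at 0.6". It arrives at 116 evaluable patients and recruits 160, 40 per condition, with 20% drop-out expected.

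**The concern.** The hypothesis is directional and has one comparator: each intervention against control. The named test asks whether any of the four group profiles departs from parallel over four times. Two active arms that differ from each other would be enough to reject it, even if neither beat control. Its 9 degrees of freedom also cover differences between interventions and between T1, T2 and T3, where the hypothesis predicts less. When the interventions respond alike, the test spreads its sensitivity over directions that carry no signal.

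Two things are at stake. The claim of superiority would rest on comparisons not identified in the published plan. Depending on effect size and pattern, some power for that claim would also be given away.

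**Working it through.** **Inputs.** Alpha 0.05 two-sided, correlation ρ = 0.6, four groups, m = 4 times, and effect size 0.3, all from Recruitment and Statistical Analyses. Completers per arm: 116/4 = 29, or 40 × 0.8 = 32. Assumed: compound symmetry, complete data, one outcome at a time, and effects stable over T1 to T3 unless stated.

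**1. The plan's own figure.** For the between-factors test, λ = f²·N·m / (1 + (m − 1)ρ). With f = 0.3 and N = 116, λ = 0.09 × 116 × 4 / 2.8 = 14.91. On 3 and 112 df the power is 0.905. At N = 112, λ = 14.40 and power is 0.893. So 116 is reproduced, and 0.3 is best read as Cohen's f.

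**2. The planning effect in SD units.** With three equal arms at d and control at 0, the SD of the four means is d√3/4 = 0.433d. Setting this to 0.3 gives d = 0.69.

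**3. Degrees of freedom.** Group-by-time: (4 − 1)(4 − 1) = 9 per outcome.

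**4. Pooled contrast against omnibus.** For mean change (average of T1 to T3, minus T0) the variance is (1 − ρ)(1 + 1/3) = 0.4 × 1.333 = 0.533. For active arms pooled against control, λ = d² / [0.533 × (1/(3n) + 1/n)]. At d = 0.5 and n = 32, λ = 0.25 / (0.533 × 0.0417) = 11.25. On 1 df the power is 0.91. The same λ on 9 df (univariate form) gives 0.61, and simulated Wilks' lambda gives 0.60.

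| Equal effect, SD | n = 29: omnibus (Wilks) / pooled | n = 32: omnibus (Wilks) / pooled |
|---|---|---|
| 0.3 | 0.19 / 0.48 | 0.22 / 0.51 |
| 0.4 | 0.35 / 0.72 | 0.39 / 0.76 |
| 0.5 | 0.55 / 0.89 | 0.60 / 0.91 |
| 0.69 | 0.87 / 0.99 | 0.91 / 0.996 |

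With no effect, both tests reject in about 5% of simulations.

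**5. Other patterns.**
- Arms at 0.4/0.5/0.6 SD, n = 32: 0.65 omnibus, 0.91 pooled.
- Arms at 0.3/0.5/0.7 SD, n = 29: 0.75 (univariate 9 df) and 0.89.
- Arms at 0.2/0.5/0.8 SD, n = 29: 0.89 and 0.89, so no gap.
- Effect growing as 0.6, 0.8 and 1.0 of d over T1 to T3, n = 29: gap of 17 to 32 points for d from 0.3 to 0.6.
- The 3 df between-group test that was actually sized, at f = 0.3 and N = 116: 0.905, against 0.97 for its 1 df contrast, a gap of 6 points.

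**6. Power per arm, all on mean change.** This is the like-for-like comparison for showing that a given intervention beats control. The planned procedure is three contrasts at 0.05/3. The comparator is six-pair Bonferroni tests made only after a significant MANOVA.

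| Equal effect, SD | n per arm | Three planned contrasts | Gated six-pair tests |
|---|---|---|---|
| 0.5 | 32 | 0.62 | 0.44 |
| 0.69 | 32 | 0.91 | 0.83 |
| 0.69 | 29 | 0.88 | 0.78 |

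For the first row, the planned contrast has noncentrality 0.5 / (0.730 × √(2/32)) = 2.74, where 0.730 = √0.533. Adding the gate alone to the three planned contrasts costs about 14 to 15 points at 0.5 SD and 5 to 6 at 0.69 SD (n = 32).

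**The case against.** The strongest reply has four parts.

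- **The large gap belongs to the pooled contrast.** That contrast cannot show that each intervention beats control. Three contrasts at 0.05/3 have per-arm power of 0.62 at 0.5 SD with 32 per arm, hardly above the omnibus test's 0.60. The arithmetic is right, but the two figures describe different events: rejecting the omnibus null establishes nothing about any one arm. The comparison in step 6 is the relevant one, and a smaller gain remains there.
- **The gate is not written.** The text says that post hoc comparisons follow the MANOVA. A reader might infer that superiority is lost whenever the omnibus test fails; that is a common convention but not stated. The six pairs and the Bonferroni adjustment are likewise assumed. This stands, so the step 6 figures are conditional.
- **The omnibus test serves a stated purpose.** The sample size is for a comparison between the four groups, and the Introduction wants SICT compared with hypnosis and meditation. This stands as a reason to keep the MANOVA, not to let it carry the superiority claim.
- **A condensed article may leave contrasts to the full plan.** This is fair for the details of the post hoc tests. But the article does name its test, and that test addresses a different question from its main hypothesis.

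**Conclusion.** The point holds in a limited form. The named test does not match the superiority hypothesis, and the article fixes no active-versus-control contrast as confirmatory. That much needs no assumption about effect size.

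The power cost depends on the scenario. Under equal, stable effects with ρ = 0.6 and 29 to 32 completers per arm, the omnibus test trails a pooled contrast by about 30 to 37 points at 0.3 to 0.5 SD, and by about 8 to 13 points at the planning effect of about 0.69 SD. The gap closes if the arms differ as widely as 0.2/0.5/0.8 SD. For each arm, the gain from planned contrasts is about 18 points at 0.5 SD (0.62 − 0.44) and 8 to 10 at 0.69 SD, if the post hoc tests are gated and adjusted over six pairs.

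Two stronger readings are not supported. A reader might infer a general loss of about 30 points whenever all three interventions work. That needs near-equal effects smaller than the planning effect, and the documents fix neither condition. At the planning effect the omnibus test would miss in only about 9% to 13% of trials. A reader might also infer that per-arm power is roughly halved, by setting planned mean-change contrasts against gated six-pair tests at T1 alone (0.63 against about 0.30 at 0.5 SD). Much of that difference comes from dropping T2 and T3, which the protocol does not propose.

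**What to change.** In Statistical Analyses, name three active-versus-control contrasts on change from T0, averaged over T1 to T3, as the confirmatory superiority tests for each primary outcome. Share alpha across the three (for example 0.05/3 each), and state that they do not depend on the MANOVA result. Keep the MANOVA and the comparisons between interventions as supportive.

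This changes wording only and needs no new data or patients. The price is that differences between interventions and the shape of the profiles become secondary. Averaging over T1 to T3 suits the stated expectation of a stable or growing effect; contrasts at T1 alone would give up much of the gain (0.42 per arm at 0.5 SD with 32 per arm, against 0.62).
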